### Subjects and study population

#### Inclusion criteria

Adult patients (age > 18 years) undergoing to general anesthesia and mechanical ventilation for elective major open abdominal surgery (gastrointestinal, urologic, gynecologic and vascular surgery)Expected duration of surgical procedure higher than 120 minASA-PS Classification II-III-IVPlanned postoperative ICU/HDU admission

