### Statistical analysis

Analysis will be performed on intention-to-treat basis.

Data will be checked for normal distribution using Kolmogorov-Smirnov test and presented as mean and standard deviation or as median and interquartile range as appropriate.

The primary end point is the difference of postoperative complication rate between the two group of patients. It will be evaluated using Fisher’s exact test or Pearson’s Chi square test as appropriate. Non-inferiority of experimental protocol respect to control group will be confirmed if the difference (including 95% confidence interval) will be lower than non-inferiority margin established at 10%. The 10% margin was chosen because it represents a two-thirds proportion of lower expected beneficial effect of PGDT (considering higher 95%CI for RR of 0.85) to reduce postoperative complications in comparison with conventional fluid therapy (RR 0.76 [CI95% 0.68–0.85]) [17].

Student t test or Mann–Whitney U test will be used to analyzed secondary outcomes as appropriate. Mortality between groups will be analyzed using the Kaplan-Meier method. The Log Rank test will be used to evaluate the statistical significance. Cox regression model using forward selection method for entering explanatory variables will be used to perform multivariate analysis. The age, type of surgery, ASA-PS classification and comorbidities will be considered as variables. A *p* value of F-test < 0.05 will be considered for variable inclusion. The amount of multicollinearity in the model will be estimated by the variance inflation factor (VIF). A VIF higher than 4 will be considered a sign of multicollinearity. Predicted R^2^ will be used to assess overfitting.

An interim analysis will be performed by independent statistician when 50% of information will be available (100 patients recruited). To monitor for harm or futility, the one-sided *p* value is calculated for testing the hypothesis HR = 1 versus the alternative HR > 1 (meaning the experimental treatment is doing worse than the standard treatment). If the *p* value is < 0.0394 at a monitoring time, then the trial would stop with the conclusion that non-inferiority cannot be claimed [18, 19]. Stopping rule for efficacy has not been defined [20].

For each statistical test, a *p* value < 0.05 is considered statistically significant.

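### The Cox model, by position in the text for 28-day mortality, has a linear-regression entry rule and overfitting check, and selects covariates on what are probably few deaths without naming the randomised arm

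*Protocol article*

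**What the plan says.** Mortality at day 28 is a secondary outcome (protocol article, Objectives). In the Statistical analysis section the comparison of arms comes first: "Mortality between groups will be analyzed using the Kaplan-Meier method", with a log-rank test for significance. The next sentence introduces the model: "Cox regression model using forward selection method for entering explanatory variables will be used to perform multivariate analysis".

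The details of the model follow:

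- Candidates: "The age, type of surgery, ASA-PS classification and comorbidities will be considered as variables". The allocated protocol is not listed and is not said to be forced in.
- Entry rule: "A *p* value of F-test < 0.05 will be considered for variable inclusion".
- Collinearity: a variance inflation factor above 4 is taken as a warning sign.
- Overfitting: "Predicted R^2^ will be used to assess overfitting".

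The article gives no expected mortality, no expected number of deaths and no statement of what the model is meant to estimate.

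**The concern.** The entry rule and the overfitting check do not belong to the model they are attached to. This is a stated rule that is wrong, not a detail left to a fuller document. Whoever runs the analysis must substitute another entry test and another check. If that choice is made after the data are seen, the covariate set is no longer pre-specified.

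Two further points bear on the usefulness of the model. Forward selection by p-value reports intervals as if the chosen covariates had been fixed in advance, which makes them too narrow, and this is worse when events are few. And because the arm is not among the listed variables, the text does not say whether the final model contains a treatment effect at all.

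What is at stake is any adjusted hazard ratio for a secondary outcome.

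**Working it through.** **1. Do the tools fit the model?** The documents' rules set against the standard Cox model:

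| Stated tool | Where it is defined | Usable for a standard Cox model? |
|---|---|---|
| F-test for entry | Ratio of mean squares from least-squares residuals | No; entry uses a score, Wald or likelihood-ratio test |
| Predicted R² | Leave-one-out squared prediction error in linear regression | No; optimism would need another method, such as a bootstrap |
| Variance inflation factor | Covariates only | Yes |

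**2. Candidate parameters.** Inputs: four surgery categories, "elective major open abdominal surgery (gastrointestinal, urologic, gynecologic and vascular surgery", and three ASA classes, II to IV (both Inclusion criteria); a comorbidity list that names four examples and ends open (Data collection).

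- ASA categorical, each named comorbidity separate: 1 (age) + 3 (surgery) + 2 (ASA) + 4 (comorbidities) = 10, and more if the open list is extended.
- ASA as a linear score, comorbidity as a single score: 1 + 3 + 1 + 1 = 6.

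**3. Deaths per parameter.** The plan has no mortality figure to reproduce. The only figure taken from it is the 200 patients to be enrolled (Sample size calculation). Mortality is an assumption, shown over a range. Deaths = 200 × mortality.

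| Assumed 28-day mortality | Deaths | Per parameter, 10 parameters | Per parameter, 6 parameters |
|---|---|---|---|
| 1% | 2 | 0.2 | 0.3 |
| 2% | 4 | 0.4 | 0.7 |
| 3% | 6 | 0.6 | 1.0 |
| 5% | 10 | 1.0 | 1.7 |
| 8% | 16 | 1.6 | 2.7 |
| 10% | 20 | 2.0 | 3.3 |

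For orientation, five deaths per parameter with 10 parameters needs 50 deaths (50/200 = 25% mortality), and ten needs 100 (50%). Even if the four named terms cost one parameter each, ten per term needs 40 deaths (20%).

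**4. False entry.** With k independent noise terms tested at 0.05, the chance that at least one enters is 1 − 0.95^k. This gives 18.5% for k = 4, 26.5% for k = 6 and 40.1% for k = 10.

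**5. Simulation of the first selection step.** Settings: 200 patients, 10 one-parameter noise terms, Cox score tests, 4,000 runs per setting. Assumed distributions: surgery 40/20/20/20%, ASA 50/40/10%, comorbidities at 10 to 20%. At least one noise term met the 0.05 level in 35% to 38% of runs across 4 to 20 deaths. The share of runs in which at least one binary level held none or all of the deaths, so that its hazard ratio would be infinite or zero if entered, was:

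| Deaths | Share of runs |
|---|---|
| 4 | 99.8% |
| 6 | 98% |
| 10 | 85% |
| 16 | 52% |
| 20 | 35% |

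**The case against.** The strongest reply is that this is a slip of terminology in a supplementary analysis. Software would use a score or likelihood-ratio test where the article says F-test, and the model would then run. That is fair as far as it goes, and a reader should not infer that a forward-selected Cox model is impossible. But the article names a specific test and a specific check, both wrong, and predicted R² has no standard Cox counterpart to slip into its place.

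Second, the scarcity of deaths is not in the documents. This stands: it is an assumption and is shown as a range. A reader might infer from it that the model would be unusable. The documents do not support that, and near 20 deaths unreliable is the accurate word.

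Third, the parameter count depends on coding. This stands too, which is why 6 is shown beside 10.

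Fourth, the Cox sentence does not name its outcome. If it meant complications, the planned rates of 28% and 35% would give 28 + 35 = 63 events in 200 patients, or 6.3 to 10.5 per parameter, and the argument from few events would largely fall. Mortality is the natural reading, because the sentence follows directly on Kaplan-Meier and log-rank, and complications are assigned to Fisher's exact or chi-square tests. The wrong entry rule and overfitting check would remain on either reading.

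Fifth, the model may be a search for prognostic factors, and a condensed article may leave the role of treatment to the full protocol. The text allows this. It means only that an adjusted treatment effect is not clearly promised, so the purpose should be stated.

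**Conclusion.** The point holds, within a secondary analysis. The F-test entry rule and the predicted R² check are not defined for the standard Cox partial likelihood and cannot be applied as written; this part rests on no assumption. The weakness of the selection rests on two: that the model is for 28-day mortality, and that mortality lies between 1% and 10%. On those, deaths per candidate parameter run from about 0.2 to 3, and with 10 noise terms the chance of at least one false entry is about 35% to 40%. An adjusted hazard ratio from such a model, with its interval, would be unreliable.

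A reader might go further and infer that the trial's mortality comparison is compromised. It is not: Kaplan-Meier and log-rank carry that comparison and do not depend on the Cox model. The complication endpoint and its non-inferiority rule do not use it either. The text should be corrected before analysis, but the main conclusion of the trial does not turn on it.

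**What to change.** - Delete the forward selection, the F-test criterion and the predicted R² check.
- Keep Kaplan-Meier and log-rank as the mortality comparison, and add the 28-day risk difference between arms with its 95% confidence interval.
- If a Cox model is kept, name its outcome and purpose and label it exploratory. Force treatment in, with at most one or two pre-specified covariates (age, for example). Use likelihood-ratio tests, and a Firth-penalised fit if deaths are few.

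Adding covariate adjustment to the complication endpoint is not needed to cure this error.

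The cost is a change of wording and fewer covariates examined in a secondary analysis. No data collection or sample size changes. Recruitment was still under way when the article was submitted (Trial status), so the change could be made before the analysis.

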### Adverse events

All adverse events (AE) will be recorded in the hospital notes in the first instance. A record of all AEs, whether related or unrelated to the treatment will also be kept in the CRF. If the Investigator suspects that the disease or condition has progressed faster due to the intervention, then he will report this as an unexpected adverse event to the sponsor. Only deaths that are assessed to be caused by the trial intervention will be reported to the Sponsor. This report will be immediate.

Considering the safety profile of the interventions applied in this study (PGDT protocols that showed a benefit to reduce postoperative complication rate without significant adverse effects), we believe that institution of a safety committee is not mandatory.

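### The interim harm/futility rule tests a hazard ratio with no named event, while the primary endpoint is a difference in proportions, and its null takes no account of the 10-point margin

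*Protocol article*

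**What the plan says.** All in the Statistical analysis section of the protocol article, unless noted:

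- Endpoint: "The primary end point is the difference of postoperative complication rate between the two group of patients".
- Test: "It will be evaluated using Fisher’s exact test or Pearson’s Chi square test as appropriate".
- Final criterion: non-inferiority "will be confirmed if the difference (including 95% confidence interval) will be lower than non-inferiority margin established at 10" percent.
- Interim timing: "An interim analysis will be performed by independent statistician when 50% of information will be available (100 patients recruited").
- Interim purpose: the sentence opens "To monitor for harm or futility, the one-sided" p value, which "is calculated for testing the hypothesis HR = 1 versus the alternative HR > 1".
- Consequence: if the p "value is < 0.0394 at a monitoring time, then the trial would stop with the conclusion that non-inferiority cannot be claimed".

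There is no stopping rule for efficacy. Kaplan-Meier and log-rank methods are assigned to mortality only, and the Objectives section lists mortality at day 28 as a secondary outcome. The document defines no time-to-complication variable and no hazard ratio for complications.

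**The concern.** A stopping rule needs an endpoint, a scale, a null value and a consequence that belong together. Here the consequence is a statement about non-inferiority, which the protocol defines only for complication rates on the risk-difference scale. The test is on the hazard-ratio scale with no event attached. The independent statistician would have to guess the event, or use the one outcome that has a survival analysis and draw a conclusion about a different outcome.

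The null value is a second, separate problem. The rule is meant to cover futility as well as harm. Futility in this trial means that the final interval is unlikely to fall below 10 points. A test of no difference does not ask that question, whichever scale is used. A trial with almost no prospect of success could therefore pass its only planned look.

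**Working it through.** **1. The statements side by side**

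| | Primary analysis | Interim rule |
|---|---|---|
| Event | any complication in hospital | not named |
| Scale | difference in proportions | hazard ratio |
| Reference value | 10-point margin | HR = 1 (no difference) |
| Conclusion | non-inferiority or not | non-inferiority cannot be claimed |

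The last row concerns the same claim. The three rows above it do not match.

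**2. Inputs**

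From the Sample size calculation section: rates of 28% and 35%, margin 10 points, 92 per group needed, 100 per group enrolled. From the Statistical analysis section: threshold 0.0394, a look at 100 patients (about 50 per arm), 95% confidence interval. My assumptions: pooled rate (28 + 35)/2 = 31.5%, and all 100 per arm evaluable at the end.

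**3. The plan's own figures**

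The 92 per group reproduces as (1.645 + 0.842)² × (0.28×0.72 + 0.35×0.65) / 0.17² = 91.8. This needs one-sided 0.05 and an experimental arm 7 points better than control (0.10 + 0.07 = 0.17). That is a separate matter from this point, but it is why I use both equal rates and a 7-point benefit as future effects below. The 0.0394 cannot be derived from anything in the document. It corresponds to z = 1.758.

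**4. Where the rule stops if run on complications**

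Interim SE = √(2 × 0.315 × 0.685 / 50) = 0.0929. Boundary = 1.758 × 0.0929 = 0.163, an observed excess of about 16 points. In whole patients, with 14/50 control events, 22/50 gives p = 0.048 (continue) and 23/50 gives p = 0.031 (stop), so the excess must reach 18 points. With 19/50, an excess of 10 points, p = 0.144 and the trial continues.

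**5. Conditional power for final non-inferiority**

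Final SE = √(2 × 0.315 × 0.685 / 100) = 0.0657. Success needs an observed difference below 0.10 − 1.96 × 0.0657 = −0.0288. The final difference is the mean of the two halves, so after an interim difference d the second half must show less than 2(−0.0288) − d. With a true difference θ in the second half:

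CP = Φ[(−0.0575 − d − θ) / 0.0929]

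| Interim difference d | θ = 0 | θ = −0.07 |
|---|---|---|
| 0 | 27% | 55% |
| +0.10 | 4.5% | 17% |
| +0.163 (boundary) | 0.9% | 5% |

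Before any data, the chance of success is Φ(−0.0288/0.0657) = 33% under equal rates.

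**6. Chance of stopping, by scale**

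Control rate 28%, 50 per arm. Proportions: exact enumeration of the pooled z test. Hazard ratio for time to first complication (not defined in the document): HR = ln(1 − pE)/ln(1 − pC), events D = 50(pC + pE), power Φ[√(D/4) ln HR − 1.758].

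| True excess | Proportions | Hazard ratio |
|---|---|---|
| 0 | 4% | – |
| 7 points | 15.5% | 16% (HR 1.31) |
| 10 points | 24% | 25% (HR 1.46) |
| 20 points | 63% | 64% (HR 1.99) |

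The scale makes almost no difference to these probabilities.

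**7. If the rule is run on deaths**

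The document gives no mortality rate. Over an assumed range of 1–8%, 100 patients yield 1–8 deaths if HR = 1. If the true HR is 2, expected deaths rise to between 1.5 and 11.7 and the same power formula gives 9% to 28%. With three deaths all in the experimental arm, the log-rank approximation gives z = √3 = 1.73 (p = 0.042), below the cut. With four it gives z = 2 (p = 0.023), which crosses, whereas an exact split test gives 0.5⁴ = 0.0625, which does not.

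**The case against.** The strongest reply is that the hazard ratio is loose wording. Non-inferiority is defined only for complications, so the natural reading is a complication comparison, and step 6 shows that the operating characteristics are then nearly the same on either scale. That stands as far as it goes: it makes the mortality reading the less natural one. It does not supply the missing event, and it does not touch the futility point, because the null stays at no difference.

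Four stronger readings are tempting and should not be drawn.

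- **The hazard ratio makes the rule blind to harm.** It does not. The 24% chance of stopping at a 10-point true excess comes from 50 per arm and the 0.0394 cut. Putting the same test on proportions leaves it unchanged, and a 20-point excess is caught about 63% of the time.
- **All other safety routes are closed.** The Adverse events section does say "Only deaths that are assessed to be caused by the trial intervention will be reported to the Sponsor" and sees no need for a safety committee. But it also has all adverse events entered in the case report form whatever their relation to treatment, and day-28 mortality is collected. It does not say who attributes deaths, so attribution by unblinded staff is an inference only.
- **The look is mistimed.** The sentence can mean the data of the first 100 patients. Recruited patients need not yet have outcomes, but this is a matter of wording.
- **The low conditional power is all the rule's fault.** Part of it reflects the sample size: success under equal rates has only a 33% chance at the outset. What stands is that the rule does not look at this quantity at all.

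**Conclusion.** The point holds. The only stopping rule in the document is stated on a scale that the primary endpoint does not have, with no event named, and its conclusion concerns an outcome that its test does not identify. As a futility rule it is tied to the wrong reference value: at an observed excess of 10 points it lets the trial continue with conditional power of about 4.5% under equal rates, and it stops only near 16 points, where that figure is about 1%.

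These figures assume a pooled complication rate of 31.5%, 50 per arm at the look, 100 per arm at the end, a two-sided 95% interval and a normal approximation. The 4.5% also depends on the assumed future effect: with a 7-point benefit from then on it would be 17%. Death counts rest on a mortality rate that the document does not give. The mismatch of endpoint, scale and null needs none of these assumptions. The final estimate and type I error of the trial are not affected.

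**What to change.** Amend the interim paragraph before the look is run:

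1. **Harm.** State the test on the primary endpoint as a risk difference: a one-sided test of equal complication proportions, keeping 0.0394 if the sponsor wishes. This repairs the definition and leaves the chance of detecting harm as it is.
2. **Futility.** Add a non-binding check of conditional power for the final 95% interval against the 10-point margin, with the threshold and the assumed future effect fixed in advance.
3. **Timing and data.** Trigger the look when 100 patients have a complete primary outcome, and show the independent statistician deaths by arm.

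The cost is a short amendment, minor programming and some possible loss of power from item 2, if its advice is followed. The choice of threshold matters. With CP assessed under equal rates on the inputs above, a 20% threshold flags any interim difference above −0.0575 + 0.842 × 0.0929 = +0.021. That happens in 1 − Φ(0.021/0.0929) = 41% of trials with equal arms, and in 1 − Φ[(0.021 + 0.07)/0.0929] = 16% of trials with a true 7-point benefit. A 10% threshold flags differences above −0.0575 + 1.282 × 0.0929 = +0.062, which gives 25% and 8% in the same way. Many flagged trials would have failed anyway, so the power lost is smaller than these shares, but a strict threshold does cost some. There is no inflation of type I error, because the trial has no efficacy stop.

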## Discussion

The role of perioperative hemodynamic optimization has been clearly shown by literature and the current spreading of mini-invasive monitoring systems able to estimate CO permits an easier application of these protocols than occurring in the past when only invasive techniques (e.g. pulmonary artery catheter) were available. As a predefined target of CO or DO_2_ seems to be not adequate for every patient, a personalized therapy is likely more appropriate. Following this concept, dynamic parameters of fluid-responsiveness (PPV and SVV) allow to titrate fluid administration aiming an increase of CO as a consequence of preload optimization but avoiding fluid overload. This approach has the advantage of personalized fluid therapy, but it does not consider if CO is adequate or not because preload optimization occurs independently from parameters of tissue perfusion and oxygen consumption. A protocol based on O_2_ER considers this second important aspect. An O_2_ER higher than a predefined cutoff is reflecting an inadequate DO_2_ to tissue and consequently an inadequate CO. This condition, but not fluid-responsiveness per se, is the trigger to start hemodynamic optimization. Moreover, in this contest we believe that CVP may be useful to limit fluid administration independently from PPV or SVV value. In fact, CVP depends on several conditions including preload status but also on cardiac function and ventricular compliance. Thus, this trial aims to demonstrate that this latest strategy of perioperative hemodynamic optimization is not inferior to the former in term of postoperative complications, but it may be responsible for a lower fluid administration. We decided to conduct a non-inferiority study because PGDT is routinely applied in this kind of patients due to the demonstrated benefits on outcome. Thus, small difference in reduction of postoperative complication rate between two different PDGT protocols seems reasonable.

Methodologically, the main limitation of this trial is the inability to blindly administer the interventions. However, this point is not clinically resolvable in this research field. Moreover, if participation of several centers may increase enrollment rate and may potentially extend the applicability of results, on the other hands too few patients per center may increases heterogeneity.

## Trial status

Protocol version 2.0 of 26.06.2019. At the date of manuscript submission, the patients’ recruitment process is ongoing. It is expected that the recruitment will be complete within December 2021. The results of this study have not already been published or submitted to any journal.

